## Abstract

**Methods::**

This is a prospective randomized, a single-blind, sham-acupuncture controlled trial to study the clinical efficacy of acupuncture combined with Western medicine in the treatment of mild to moderate AD. Participants will be randomly divided into treatment and control groups. The treatment group using acupuncture combined with donepezil hydrochloride orally, and the control group using sham acupuncture combined with donepezil hydrochloride orally, followed up for 24 weeks after 24 weeks of continuous treatment. Outcome measures included: AD assessment scale-cognitive subscale, mini-mental state examination, activities of daily living, neuropsychiatric inventory questionnaire, serum superoxide dismutase, and homocysteine levels. Finally, SPASS 21.0 software was used for statistical analysis of the data.

**Discussion::**

This study will evaluate the efficacy of acupuncture combined with Western medicine in improving cognitive function and activities of daily living in AD patients. The results of this study will verify whether the efficacy of acupuncture in the treatment of AD belongs to the placebo effect, which will also provide a reference for the clinical use of acupuncture combined with Western medicine in the treatment of AD.

**Trial registration::**

The TCTR identification number is TCTR20220817004.

## 1. Introduction

Alzheimer disease (AD) is a common cause of dementia, and the main clinical manifestations are aphasia, agnosia, and gradual loss of independent living ability.^[1]^ With the acceleration of the aging process of the population, the incidence rate of AD continues to rise. And the mortality rates of major diseases such as AIDS, stroke, and heart disease in the elderly in the United States have decreased over the past 15 years, with only AD increasing by 71%.^[2]^ The onset of the disease is insidious and progressively aggravated, generally with obvious symptoms after 2 to 3 years of onset, gradual memory, cognitive dysfunction, and behavioral abnormalities, and death due to complications such as pulmonary and urinary tract infections and pressure sores 10 to 20 years after onset.^[3]^ The pathogenesis of this disease is complex, and there is no effective drug that can reverse the disease process.^[4]^ It is important to take timely and effective therapeutic drugs and measures to delay the development of the disease.

Although researchers have made great efforts for the study of AD, there is no specific therapeutic drug at present. Cholinesterase inhibitors and memantine are drugs approved by the Food and Drug Administration and European Agency for the Evaluation of Medical Products for the treatment of AD, and although they can improve cognitive function and delay the disease in patients,^[5]^ they are not effective alone and have adverse effects on long-term use.^[6]^

Acupuncture and moxibustion are traditional treatments in China and are widely used in clinical practice. In the treatment of AD, it has the characteristics of multiple levels, multiple pathways, and multiple targets, and the advantages of reliable efficacy and few side effects.^[7,8]^ Recent systematic reviews have shown^[9,10]^ that acupuncture combined with Western medicine is superior to Western medicine alone in improving cognitive function and activities of daily living in AD patients. At the same time, these systematic reviews also point out that there are serious methodological shortcomings in current randomized controlled trials on acupuncture treatment of AD, such as randomization problems, lack of sample size estimation, and no blind method.^[9–11]^ These deficiencies also lead to a low strength of evidence for the research results, limiting the application of acupuncture in AD. Limited by acupuncture treatment modalities, strict double-blind cannot be achieved in clinical practice,^[12]^ and whether its clinical efficacy belongs to the placebo effect is controversial.^[13,14]^ At present, domestic and foreign scholars are continuously exploring the optimization of placebo acupuncture in order to explore the specific effect of acupuncture.^[15]^ This study will study the clinical efficacy of acupuncture combined with Western medicine in the treatment of mild to moderate AD by randomized, single-blind, placebo acupuncture parallel control method.

## 2. Materials and Methods

### 2.1. Study design

This is a prospective, randomized, single-blind, sham acupuncture controlled trial to study the clinical efficacy of acupuncture combined with Western medicine in the treatment of mild to moderate AD. Participants will be randomly divided into treatment and control groups. The treatment group will receive oral donepezil hydrochloride combined with acupuncture treatment, and the control group will receive oral donepezil hydrochloride combined with sham acupuncture treatment. After 24 weeks of continuous treatment, the participants will be followed up for 24 weeks. Flow diagram is shown in Figure 1, and study schedule is shown in Table 1. This experiment will follow the standard for reporting intervention in acupuncture controlled trials^[16]^ and the standard for reporting comprehensive trials.^[17]^

**Table 1 T1:** Study schedule.

Project	Stage				
	Screening period	Treatment period		Follow-up	
	Baseline	12-wk	24-wk	12-wk	24-wk
Record fill	√				
Fulfill inclusion criteria and exclusion criteria	√				
Sign informed consent	√				
Random allocation	√				
Treatment	√	√	√		
Effectiveness observation					
ADAS-Cog	√	√	√	√	√
MMSE	√	√	√	√	√
ADL	√	√	√	√	√
NPI	√	√	√	√	√
SOD and Hcy	√	√	√	√	√
Safety evaluation					
Blood test and urinalysis	√		√		√
Liver and kidney function	√		√		√
Record of adverse event		√	√	√	√

ADAS-Cog = Alzheimer disease assessment scale-cognitive subscale, ADL = activities of daily living, Hcy = homocysteine, MMSE = mini-mental state examination, NPI = neuropsychiatric inventory questionnaire, SOD = serum superoxide dismutase.

**Figure 1. F1:**
[figure not shown]
Flow diagram.

### 2.2. Ethics and registration

The study protocol will be conducted in accordance with the Declaration of Helsinki and Ethical Guidelines for Clinical Research. This study has been reviewed by the Clinical Research Ethics Committee of our hospital and registered on the Thai Clinical Trials Registry (registration number: TCTR20220817004). Before randomization, all patients were asked to sign an informed consent form and were given the option whether to continue the trial at any time.

### 2.3. Patients

#### 2.3.1. Diagnosis basis.

The diagnostic standard for AD refers to the diagnostic standard for AD established by the National Institute on Aging-Alzheimer’s Association workgroups on diagnostic guidelines for AD in the United States.^[18,19]^ TCM diagnostic standard refers to Chinese disease diagnostic efficacy standards.^[20]^

#### 2.3.2. Inclusion criteria.

Meet the diagnostic standard of Alzheimer disease.Aged ≥50 years old and ≤85 years old.Patients with mild to moderate Alzheimer disease (dementia degree judged as mini-mental state examination score 10–23 points)^[21]^.Patients recognize the study protocol and sign the informed consent form.

#### 2.3.3. Exclusion criteria.

There are other diseases that may lead to dementia besides Alzheimer disease.Acute cardiovascular and cerebrovascular events (such as unstable angina pectoris, myocardial infarction, stroke, etc.) occurred within 3 months before screening.There was skin ulceration at acupuncture points.Refusal or fear of acupuncture.Those who have participated in or are participating in other clinical trials within the past 1 month.

#### 2.3.4. Standard for failing off and suspension.

The patient withdrew from the study for any reason.The principal investigator considered that the subject was not suitable for continuing the study.The subjects had poor compliance and changed the drug or added unspecified therapeutic drugs by themselves, which had an impact on the study results.Serious safety events occurred during the study and were assessed to be inappropriate for continuing the study.The patient was accidentally included after misdiagnosis or did not meet the inclusion and exclusion standard.

For all dropouts and patients who discontinue the trial, we will complete the last data test as far as possible. The dropout reasons and handling methods for all dropouts will be recorded on the case report form (CRF).

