### 2.6. Intervention measures

Based on the recommendations of the EFNS guidelines for the diagnosis and management of Alzheimer disease,^[23]^ patients in two groups will receive oral donepezil hydrochloride 5 mg at bedtime (Weicai Pharmaceutical Co., Ltd., Shanghai, China, GYZZ H20050978, 5 mg/tablet) once a day for 24 weeks.

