### 2.10. Statistical analysis

The study results will be independently analyzed by Full Analysis Set and Per-Protocol Set, and the safety evaluation will be based on Safety Set. Statistical evaluation of Full Analysis Set will follow intent-to-treat. Missing values will be measured using the last observation carried forward method. Data from this study will be statistically analyzed using SPSS 21.0 software (IBM Company, New York, NY). Count and grade data were expressed as percentage (%), the measurement data of *χ*^2^ test or non-parametric test were expressed as mean ± standard deviation (*x* ± S) or interquartile range M (P25, P75), normal distribution was analyzed by *t* test, skewed distribution was analyzed by non-parametric test, and One-way analysis of variance multiple comparisons were used between multi-point repeated data groups, and differences were considered statistically significant when *P < *.05.

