## 3. Discussion

AD is a chronic progressive neurodegenerative disease characterized by cognitive impairment such as memory impairment and personality changes.^[7]^ Modern studies have found that abnormal cholinergic neurons in the basal forebrain leading to decreased acetylcholine function in the hippocampus are the main pathological factors causing AD, but also cause behavioral and cognitive changes in patients, causing memory and orientation decline.^[28]^ Donepezil hydrochloride is a second-generation specific reversible central acetylcholinesterase inhibitor, which can inhibit acetylcholoyl hydrolysis, improve cognitive function, and alleviate hippocampal atrophy in patients.^[29]^ Clinical studies have found limited efficacy of donepezil hydrochloride alone in the treatment of AD and advocate the use of combined therapeutic regimens.^[30]^

As an important complementary and alternative therapy, acupuncture has a reliable effect in improving cognition and promoting brain function recovery.^[31,32]^ Modern studies have shown that acupuncture can enhance functional connectivity between hippocampal regions and activate specific cognitive related areas of the brain.^[33]^ Acupuncture can also reduce oxidative stress response and enhance oxygen-free radical metabolism capacity.^[34]^ Although some clinical studies have shown that acupuncture is reliable in the treatment of AD. These studies are generally of low quality and lack long-term effective follow-up. This study will avoid the effect of placebo effect on the study results by means of sham acupuncture control, and we also increased the follow-up time to observe the long-term effect of acupuncture combined with western medicine on mild to moderate AD.

This study also has some shortcomings: due to the limitation of intervention methods, this study will not achieve strict double-blind, which may have a certain impact on the results; this study will be conducted in a hospital in China, so there may be regionalization of the subject population, which biases the results.

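### Section 2.3.4 merges stopping treatment with leaving the study, which conflicts with the promised follow-up of all patients and weakens the intention-to-treat analysis

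*Protocol article*

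**What the plan says.** Section 2.3.4 gives five grounds for dropout or suspension in one undivided list. Besides the patient's own withdrawal and serious safety events judged incompatible with continuing, they are:

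- investigator discretion: "The principal investigator considered that the subject was not suitable for continuing the study";
- adherence and medication: "The subjects had poor compliance and changed the drug or added unspecified therapeutic drugs by themselves, which had an impact on the study results";
- eligibility: "The patient was accidentally included after misdiagnosis or did not meet the inclusion and exclusion standard".

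The same data-collection rule then applies to all of them: "For all dropouts and patients who discontinue the trial, we will complete the last data test as far as possible". The section mentions no later scheduled visits for these patients.

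Other sections bear on this:

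- Section 2.7.2 has all patients followed for 24 weeks after treatment, with clinic assessments at follow-up Weeks 12 and 24. Table 1 schedules ADAS-Cog at both visits.
- Section 2.10 sets up a Full Analysis Set, a Per-Protocol Set and a Safety Set. "Statistical evaluation of Full Analysis Set will follow intent-to-treat", and missing values are filled by last observation carried forward (LOCF).
- Section 2.6 specifies donepezil "once a day for 24 weeks", so the follow-up period lies after the specified drug period.
- Section 3 presents the longer follow-up as a strength: "we also increased the follow-up time to observe the long-term effect of acupuncture combined with western medicine".

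**The concern.** An intention-to-treat analysis has two parts. Patients are analysed in the arm to which they were randomised, and their outcomes are collected whatever treatment they went on to take. Section 2.10 secures the first part. Section 2.3.4 weakens the second, because it makes non-adherence, self-made drug changes, investigator judgement and late-found ineligibility reasons for leaving the study rather than only for stopping treatment.

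Such removals may be related to outcome. Patients who add a drug may well be those who are doing badly. The adherence ground is itself qualified by an effect on the results, and the discretionary ground has no objective criterion. After removal, one best-effort test stands in for the remaining visits. The introduction describes the disease as progressively worsening, so a score carried forward can hide later decline.

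At stake are the credibility of the Full Analysis Set at Week 24 and the amount of real data behind the long-term claim at follow-up Weeks 12 and 24.

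**Working it through.** **1. The planned figures reproduce.** Inputs from Section 2.4: ADAS-Cog improvement 6.65 (SD 3.23) against 4.51 (SD 2.11), α = 0.05, power 90%, 10% withdrawal. Two-sided testing is assumed.

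- Difference: 6.65 − 4.51 = 2.14.
- Root-mean-square SD: √((3.23² + 2.11²)/2) = 2.728.
- The unequal-variance t test (noncentral t) gives power 0.897 with 35 per group and 0.906 with 36, so 36 per group is right.
- Allowing for withdrawal: 36/0.9 = 40 per group, 80 in total, as stated.

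The sample size is therefore not in question.

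**2. The passages side by side.**

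| Question | Section 2.3.4 | Sections 2.7.2 and 2.10 |
|---|---|---|
| Who is followed to follow-up Week 24? | Removed patients get one last test, if it can be obtained | All patients |
| Are removed patients left out of the Full Analysis Set? | Not stated | Not stated; the set follows intention to treat |
| What fills their later visits? | Nothing scheduled | LOCF |

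The first row is a conflict in the text. The second is not: nothing excludes removed patients from the Full Analysis Set. The third row is where intention to treat is weakened, since these patients stay in the analysis only through carried-forward values.

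**3. Illustration for a per-protocol or completer analysis.** Assumptions: 10% of an arm (4 of 40) are removed, every one had zero change, and they are left out of the analysis. The mean of those remaining is then the planned mean divided by 0.9.

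- Sham arm only: 4.51/0.9 = 5.01; 6.65 − 5.01 = 1.64, a fall of 0.50/2.14 = 23%.
- Acupuncture arm only: 6.65/0.9 = 7.39; 7.39 − 4.51 = 2.88, a rise of 0.74/2.14 = 35%.
- Both arms: 7.39 − 5.01 = 2.38, a rise of 0.24/2.14 = 11%.

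**4. The Full Analysis Set.** Under the same premise the zero-change patients stay in with a carried-forward change of zero. The arm means remain 6.65 and 4.51 and the difference remains 2.14, so the percentages in step 3 do not measure bias in this set.

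A different assumption gives a different answer. Suppose 10% of one arm leave before any post-baseline test, so that LOCF gives them a change of zero, but they would otherwise have reached their arm's mean.

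- Acupuncture arm: 6.65 × 0.9 − 4.51 = 1.48 (−31%).
- Sham arm: 6.65 − 4.51 × 0.9 = 2.59 (+21%).

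The result depends entirely on what removed patients would have scored, which the article cannot tell us.

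**5. Follow-up period.** The drug-change ground has no stated end date. If it applies after Week 24, a patient removed between Week 24 and follow-up Week 12, with no last test obtained, would carry the Week 24 score to both follow-up visits. If a last test is obtained, that value is carried instead. A patient removed after follow-up Week 12 already has that visit's score.

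**The case against.** A reader might infer that Section 2.3.4 contradicts the stated intention-to-treat analysis. The article does not support that. A removed patient can still be analysed as randomised, using the last test and LOCF, and the separate Per-Protocol Set is the usual place for excluding protocol violators. This objection stands: the right word is undermines, and the direct conflict is with Section 2.7.2.

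A reader might also take poor compliance alone, or a drug change alone, as grounds for removal. The text joins poor compliance, a self-made change or addition of drugs, and an effect on the results. The ground is narrower than a quick reading suggests.

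Section 2.5 keeps patients, other investigators and statisticians unaware of allocation; only the acupuncture operators know it. That makes removal driven by knowledge of the arm less likely. It does not settle the matter, because the article does not say that the operators take no part in these judgements, and blinded removals can still be related to outcome.

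The follow-up scenario is limited to the case in step 5 and assumes that the drug-change ground operates after treatment ends. It does not touch the end-of-treatment comparison on which the trial was sized.

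Finally, the definition of the Per-Protocol Set and the recording of concomitant medication may well be in the full protocol or analysis plan. Their absence from the article is not part of this point.

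**Conclusion.** The point holds in a limited form. Section 2.3.4 does not separate stopping treatment from leaving the study. It conflicts with Section 2.7.2 on who is followed, and it leaves the intention-to-treat analysis in Section 2.10 resting on carried-forward values for patients whose removal may be related to outcome.

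The size of the bias in the Full Analysis Set cannot be derived from the article. It depends on how many patients are removed, when, from which arm, and how they fare afterwards. The shifts from 2.14 to 1.64, 2.88 or 2.38 apply only to a per-protocol or completer analysis with 10% removed, all with zero change. A reader might take them as the error in the main analysis, but under that same premise the LOCF difference stays at 2.14.

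The change is worth making because outcomes that were never collected cannot be recovered by later analysis.

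**What to change.** Reconcile Sections 2.3.4, 2.7.2 and 2.10 as follows. This concerns data collection and analysis only; when treatment should stop is left to the sponsor.

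- Divide Section 2.3.4 into stopping study treatment and leaving the study.
- State that only withdrawal of consent, death or loss to follow-up ends outcome collection.
- Keep every other randomised patient on the scheduled ADAS-Cog visits to follow-up Week 24, including those who stop study treatment, change medication or are found ineligible. Analyse them as randomised in the Full Analysis Set.
- Use the compliance, drug-change and eligibility items only to define the Per-Protocol Set, judged by staff blind to arm.

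The cost is a short amendment, re-approved by the ethics committee as Section 2.9 requires, and some effort to keep a few patients attending visits that are already scheduled. The sample size of 40 per group is unaffected.

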### 2.4. Sample size

The sample size calculation in this study was based on the improvement of the score of the AD assessment scale-cognitive subscale (ADAS-Cog)^[22]^ after the end of treatment (the difference of the mean standard deviation of the ADAS-Cog score before and after treatment), referring to the results of the pretest, 6.65 ± 3.23 in the treatment group and 4.51 ± 2.11 in the control group, using the difference test, setting *α* = 0.05, *β* = 0.10. PASS15.0 (NCSS Company, Kaysville, UT) software calculated that 36 patients were needed in each group. The estimated withdrawal rate was 10%, and the total sample size required was 80 patients, 40 patients in each group.

### 2.5. Randomization and blinding

Patients meeting the inclusion and exclusion standard will be randomized in a 1:1 ratio by a central web-based randomization tool to either the treatment group (acupuncture combined with oral donepezil hydrochloride) or the control group (sham acupuncture combined with oral donepezil hydrochloride). Random sequences were generated by an independent statistician using SAS 9.3 software (SAS Institute, Cary, NC). Research assistants entered patient information on a tablet computer and were assigned a random number to complete the random assignment based on the random number. Limited by the way of acupuncture, acupuncture operators were aware of the grouping results, and patients, other investigators, and data statisticians were not aware of the grouping results.

### 2.6. Intervention measures

Based on the recommendations of the EFNS guidelines for the diagnosis and management of Alzheimer disease,^[23]^ patients in two groups will receive oral donepezil hydrochloride 5 mg at bedtime (Weicai Pharmaceutical Co., Ltd., Shanghai, China, GYZZ H20050978, 5 mg/tablet) once a day for 24 weeks.

#### 2.6.1. Acupuncture treatment.

This study will follow the international acupuncture clinical trial standard STRICTA to ensure the quality control of acupuncture treatment.^[24]^ Acupuncture points include: Baihui (GV20), Sishencong (EX-HN1), Dazhui (DU14), Shenmen (HT7), Shenshu (BL23), and Taixi (KI3).

To ensure the implementation of blinding, patients in both groups will wear eye masks during acupuncture, take the supine position, and the acupoints will be disinfected using 75% alcohol. An acupuncturist with a TCM license and at least 3 years of clinical experience will complete acupuncture treatment using a disposable stainless steel acupuncture needle (0.25 mm × 40 mm; Suzhou Hualun Medical Appliance Co., Ltd, Suzhou, China). The treatment group required acupuncture “Needling Sensation” (Deqi), and 0.5 cm non-acupoint needle insertion in the control group at a depth of 1 to 2 nn without requiring “Needling Sensation” (Deqi).^[25]^ Every other day for 30 minutes for 24 weeks.

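### Patient blinding is at risk because needling sensation is required in one arm only and operators know the allocation, so the claims to settle or avoid the placebo effect are stronger than the design supports

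*Protocol article*

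**What the plan says.** **Needling (Section 2.6.1).** For the acupuncture arm: "The treatment group required acupuncture “Needling Sensation” (Deqi"). For the control arm: "0.5 cm non-acupoint needle insertion in the control group at a depth of 1 to 2 nn", "without requiring “Needling Sensation” (Deqi"). The depth unit is unclear as printed; nothing below depends on it. Sessions last 30 minutes, on alternate days, for 24 weeks.

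**Blinding (Sections 2.6.1 and 2.5).** The stated measure aimed at what patients perceive is the mask: "To ensure the implementation of blinding, patients in both groups will wear eye masks during acupuncture". The same sentence gives both groups the same body position and skin disinfection. Section 2.5 sets out who knows the allocation: "acupuncture operators were aware of the grouping results, and patients, other investigators, and data statisticians were not aware of the grouping results".

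**Claims.** The Discussion paragraph of the abstract says the results will verify whether acupuncture's efficacy in AD is a placebo effect. Section 3 goes further: "This study will avoid the effect of placebo effect on the study results by means of sham acupuncture control". Section 3 also lists as a shortcoming that strict double-blinding is not achieved and may affect the results. It gives the intervention method as the reason and does not say that patients themselves might become unblinded.

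**The concern.** The arms differ by design in a bodily sensation, and the person producing it knows which arm the patient is in. An eye mask hides neither the sensation nor what the operator says or asks while seeking it. The measure offered to secure patient blinding therefore does not address the main difference that the patient could notice.

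Separating the specific effect of needling from the placebo effect is the question the trial sets itself. If more acupuncture patients than sham patients come to believe they are receiving the real treatment, expectation and operator attention could add to the ADAS-Cog difference. Read as Section 3 is worded, that whole difference would be reported as specific. Blinded assessment and analysis do not remove this route, because it acts through the patient before the score is taken.

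**Working it through.** **1. The passages side by side**

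| Element | Acupuncture arm | Sham arm | Hidden by the mask? |
|---|---|---|---|
| Sight of the needling | mask worn | mask worn | yes |
| Needle enters the skin | yes | yes, shallow, at non-acupoints | not needed, similar in kind |
| Deqi | required | not required | no |
| Operator knows the arm | yes | yes | no |
| Position, disinfection, schedule | no difference stated | no difference stated | not applicable |

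Two rows remain open: deqi and the operator's knowledge. They can act together, since an operator who must obtain a sensation in one arm has a reason to ask about it there and no stated reason to ask in the other.

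**2. Exposure**

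Sessions = 24 weeks × 7 days / 2 = 84. The article does not say that deqi is sought at each session; 84 is the number of scheduled contacts with an unblinded operator.

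**3. The plan's own figure**

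Inputs from Section 2.4: ADAS-Cog improvement 6.65 ± 3.23 against 4.51 ± 2.11, α = 0.05, β = 0.10, withdrawal 10%.

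- Difference = 6.65 − 4.51 = 2.14.
- Root-mean-square SD = √((3.23² + 2.11²)/2) = 2.73.
- Two-sided normal approximation: 35 per group. Noncentral t: 36 per group, with power 90.6% (Welch) or 90.7% (pooled).
- 36/0.90 = 40 per group, 80 in total.

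The stated sample size reproduces, and this point does not affect it.

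**4. What a leak would do (illustration only)**

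The documents give no blinding data, so the shift below is an assumption and is shown over a range. Suppose needling has no specific effect and lost blinding alone shifts the mean difference by a share of 2.14. With 36 per group, SDs 3.23 and 2.11 and a two-sided Welch t test:

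| Share of 2.14 | Shift (points) | Chance of P < .05 |
|---|---|---|
| 0% | 0 | 5.0% |
| 10% | 0.21 | 6.2% |
| 25% | 0.54 | 13% |
| 50% | 1.07 | 37% |
| 75% | 1.61 | 69% |
| 100% | 2.14 | 91% |

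A small leak barely matters and a large one matters a good deal. The documents do not show where in this range the trial would fall.

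**The case against.** The strongest reply is that the sham is a credible one. It penetrates the skin, and no difference between arms is stated in mask, position, disinfection or schedule. Each patient meets only one technique and has no comparison within the trial. Not requiring deqi does not mean that sham patients feel nothing. Non-operator investigators and statisticians are stated to be blinded, the primary outcome is a cognitive test rather than a symptom report, and Section 3 concedes a limit on blinding. Deqi is also part of the technique being tested, so some difference in sensation is inherent.

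Most of this stands, and it rules out stronger readings that a reader might infer:

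- *The sham cannot control placebo effects.* This does not follow; a penetrating sham controls part of expectation and attention.
- *Patients can tell their arm by feel or talk.* This is a plausible risk, not something the documents show. The article does not describe what operators say.
- *The bias can be sized.* A belief gap of 20 to 50 percentage points times a belief effect of 1 to 2 ADAS-Cog points would give 0.2 to 1.0 point, or 9% to 47% of 2.14. Both inputs would be guesses, so the range carries no weight.
- *Entry criteria add to the problem.* The exclusion "Refusal or fear of acupuncture" applies before randomization and to both arms alike, so by itself it creates no difference between them.

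It may also be said that an operator script or a blinding check could sit in a fuller protocol that a journal article condenses. That is fair, and their absence here is not the finding. The finding rests on what is stated: unqualified claims about placebo, supported by a measure that does not reach the sensation difference written into the same section. The conceded limit on double-blinding does not repair this, because it does not name patient unblinding and stands beside the claim that the placebo effect is avoided.

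**Conclusion.** The point holds as a risk to patient blinding together with an overclaim. Deqi in one arm only, unblinded operators and about 84 scheduled contacts mean that patient blinding cannot be taken as secured by the mask. The sham gives partial control of expectation, so a difference between arms would be some evidence of a specific effect, but not the unconditional proof that the abstract and Section 3 promise.

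The size of any bias cannot be derived from the documents; the table of rejection chances rests wholly on assumed shifts. The conclusion assumes only that a sensation sought in one arm, or the talk around it, may inform some patients. It does not assume that blinding fails. The change is worth making because it bears on the trial's own question and costs little.

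**What to change.** 1. **Section 2.6.1.** Require one operator script for both arms: the same contact, the same question about sensation at the same moments, and no comment on the answer. If the full protocol already has such a script, cite it. The needling in either arm is not changed.
2. **Treatment Week 24 visit.** Ask each patient one question on guessed allocation (real, sham, don't know). Report the guesses or a blinding index by arm, descriptively. Do not make attribution conditional on balanced guesses: patients who improve may guess real because they improved, so such a rule could discount a true effect.
3. **Abstract and Section 3.** Reword so that a difference is read as evidence for a specific effect, subject to the blinding result. Name possible patient unblinding among the limitations.

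**Cost.** A short operator procedure, one added question at an existing visit and two reworded passages. Guesses may reflect perceived benefit as well as lost blinding, and may be less reliable at MMSE 10–23. The sensation question needs neutral wording, since it could itself suggest to sham patients what they are missing.
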